## Abstract

**Background:**

Preventive home visits are suited for patients with reduced mobility, such as older people. Healthcare needs for older patients are expected to increase due to the extended life expectancy estimated in coming years. The implementation of low-cost, patient-centered methodologies may buffer this rise in health care costs without affecting the quality of service. In order to find the best home care model with less investment, this paper describes a study protocol comparing two models of home care for older people.

**Methods:**

We describe a quasi-experimental study that compares the outcome of two different home care models already implemented in two primary care centers in Badalona (Barcelona, Spain). The traditional model (control model) is integrated in the sense that is continuous, the same primary care center team looks after its assigned patients both at the center and in preventive home visits. The new functional home care model (study model), consisting of a highly trained team, is specifically designed to meet patient needs and give total attention to preventive home interventions. The study will start and end on the expected dates, June 2018 to October 2020, and include all patients over 65 years old already enrolled in the home care programs of the primary care centers selected. The primary endpoint assessed will be the difference in hospitalization days between patients included in both home care programs. Other variables regarding health status, quality of care and resource utilization will also be compared between the two models.

**Discussion:**

The study in progress will assess whether a functional and highly trained home care team will meet the ever-aging population needs in terms of cost and health outcomes better than a traditional, integrated one. Lessons learned from this pilot study will provide guidelines for a future model of home care based on the IHI Triple Aim: better care, better health, and lower costs.

**Trial registration:**

Registered in ClinicalTrials.gov (Identifier: NCT03461315; March 12, 2018).

## Background

The increasing life expectancy in industrialized countries correlates with a rising prevalence of chronicity, disability, and dependence, thus stressing the need for healthcare services to make progress [1, 2]. In Spain, multimorbid patients managed in a primary care setting account for 1.38% of the overall population and 5% of people older than 65 years old [3]. The increasing trend of these percentages will result in a greater use of health care resources, including medical appointments, visits to the emergency service, hospitalization, and medication [1–4]. Therefore, it is necessary to find cost-effective strategies to cover the healthcare needs of older patients.

In the last decade, various approaches to care delivery for older people have been proposed, yielding a repertoire of models that range from traditional primary care and total patient models to integrated care models [5–7]. As part of the services offered, home care (HC) programs are intended to provide health care to patients that are unable to go to a primary care center due to their medical condition or disability, thus improving their health and active independence and reducing hospitalizations [8–11]. Some of these HC programs prioritize continuity in the sense that the same medical professional team (i.e., physician and nurse) attends the patient both at home and at the primary care center. This model, often referred to as integrated HC, has the advantage of strengthening the relationship between patients and their healthcare provider but struggles with the staff’s overloaded schedule [12, 13]. Other extensively applied models are based on skilled HC teams dedicated solely to at-home interventions; this approach, known as functional HC, increases specialization of the HC team and reduces the overburden of health care professionals, but may hamper the cohesion of healthcare services [14–16]. These models were implemented with positive outcomes regarding patients’ quality of life and care delivery satisfaction. However, studies investigating the outcome of HC have yielded heterogenous results, which likely depend on multiple factors including population factors, program characteristics, and healthcare setting [15–17]. In fact, even healthcare environments were HC is well established as a reality for care of older and disabled people acknowledge that more in-depth analysis is needed to improve understanding of the role of HC in the future of health care delivery [18]. Taken together, this heterogeneity precludes the appraisal of the benefits and drawbacks of HC approach, often leading to inconclusive evidence [19].

Catalonia is the most north-eastern region of Spain, with a population of over 7.5 million people, 19% of which is older than 65 years. Here, HC programs are highly implemented, with nearly 90% of primary care units using traditionally integrated HC approaches within each provision of healthcare service, that enroll a 5% of the population older than 65 years. However, a survey of primary care professionals involved in HC programs revealed important disadvantages of this model, such as a high burden of care, time constraints, low resources and lack of coordination with other levels of care as each of the services provides HC assistance besides their center-based duties [20]. The change from a traditional integrated HC model to a functional full-time HC is expected to result in better outcomes for patients (clinical and related to the attendance experience), increased satisfaction for the professionals involved, and less use of healthcare resources. However, there is little or no evidence regarding the benefits and drawbacks of the two models when operating in the same healthcare environment. This study aims to compare two HC programs for older people applied in Catalonia: a traditional integrated HC model provided by healthcare professionals of primary care units and a specific full-time unit of medical professionals based on a functional HC model.

## Methods

### Study design

This quasi-experimental study will compare the outcome of two HC models implemented in two primary care centers in Badalona (Barcelona, Spain). The control group will consist of patients following the integrated HC model, provided by the primary care center *Gran Sol*, and the study group will consist of patients following the new HC model (hereinafter, functional HC model), linked to the primary care center *Apenins*. Both HC teams consist of a general practitioner and a nurse. In the integrated model, HC is given by the same healthcare team providing medical care at the primary care unit with an average of 1500 inhabitants assigned to each team. By contrast, in the functional model, HC is given by a healthcare team specifically trained in the management of older, frail and multimorbid patients, providing only full-time preventive home visits and connecting to other further required special provision services. Further details regarding the characteristics of each model are shown in Table 1. The rationale for choosing these two centers relates to the balanced demographic characteristics of the reference population (Table 2).

**Table 1 Tab1:** Main characteristics of the two investigated models

Integrated HC		Functional HC
Characteristics of the healthcare team		
**Team composition**	Nurse and family doctor.	
**Team function**	The same healthcare team provides HC and manages patients in the primary care center.	The healthcare team is dedicated exclusively to HC.
**Interprofessional communication**	Healthcare professionals are part of the healthcare team regularly managing patients in the primary care center.	Although not managing patients in the primary care center, the HC team is part of the health care staff of the center and their members participate in the center meetings as specialists.
**Training**	• Regular training of family doctors, including regular stays at mental health and geriatrics units. • Regular training of nurses.	• Regular training of family doctors, including regular stays at mental health and geriatrics units. • Nursing staff receives additional training regarding the management of chronic patients, fragility, and palliative care.
**Type of professional in each visit**	Nurse, family doctor or both	
Services and visit schedule		
**Preventive visits**	• Visits of nursing staff scheduled based on the monitoring requirements of each disease as established by local guidelines. • Visits of physician scheduled at physician’s discretion based on the disease progression and clinical status of patients.	
**Non-urgent acute visits**	The patient calls the center and the physician available at that moment (not always the one regularly visiting the patient at the primary care center) visits the patient at home.	• During working hours: the patient contacts directly the physician of the HC team. • Outside the working hours: the patient calls the center and the physician available at that moment (not always the one regularly visiting the patient at the primary care center) visits the patient at home.
**Urgent visits**	The patient calls the emergency service; an emergency team and an ambulance are deployed to patient’s home.	
**Financial approach**	All visits are fully covered by the public health system.	

*HC* home care

**Table 2 Tab2:** Characteristics of the participating centers

	Integrated HC (PC Gran Sol)	Functional HC (PC Apenins)	***P***^a^
Location	Badalona, Catalonia, Spain	Badalona, Catalonia, Spain	
Professional profile	MDs and nurses specialized in family medicine	MDs and nurses specialized in family medicine	
Reference population^b^, *No.*	19,442	19,043	
Over-Aging index^c^, *%*	11%	9.2%	< 0.001
Foreign population^d^, *n (%)*	3499 (17.9%)	3046 (15.9%)	< 0.001
≥65 years old, *n (%)*	3480 (17.9%)	2970 (15.6%)	< 0.001
GMA, *adjusted indicator (IC95%)*	1.189 (1.173–1.206)	1.178 (1.161–1.195)	–
Mortality, *annual ‰*	7	5.7	0.143
IT application	eCAP	eCAP	

*HC* Home Care, *GMA* Adjusted Morbidity Groups [21]; *IT* Information Technology, *MD* Medical Doctor, *PC* Primary Care

^a^Differences between PC Gran Sol and PC Apenins

^b^Data from Msiq (Generalitat de Catalunya©), period between January and December 2015

^c^The number of persons aged 74 or over per total of persons over 64 years old

^d^The number of subjects with a foreign nationality

After signing the consent form to participate in the study during a preventive home visit, patients (or their caregivers) are provided with a set of self-administered questionnaires and scales, as well as a return envelope. In the case of patients with cognitive impairment, the documents are delivered to the caregiver. Investigators will contact study patients by phone every 6 months and ask them about their admissions to other centers than the assigned primary care center. At the end of follow-up (i.e., 2 years), study patients (or their caregivers) will be provided with the same self-administered questionnaires and scales given at baseline in a final preventive home visit (Fig. 1). Clinical and demographic data will be retrieved from patients’ medical records. All the information retrieved from the three sources (i.e., questionnaires/scales, check-up phone calls, and medical records) will be recorded in a clinical report form specifically designed for the study. Before the baseline visit, all investigators will participate in two training sessions on the scales and questionnaires used in the study.

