### Statistical analysis

The sample size calculation was based on an incidence of hospital admission of 40% and a reduction of 10% in the study group, a 2-year follow-up, and a 1:1 ratio for control and intervention groups. Under these constrains, a fixed alpha and beta errors of 5%, yielded an estimated size of 581 subjects per group. The statistical power of this sample, assuming alpha and beta errors of 5% was 85.3%.

All collected variables will be described for the overall study sample and for both study groups. Quantitative variables will be described as the mean and standard deviation (SD), and as the median and interquartile range (IR) for normally- and non-normally distributed variables, as confirmed by the Kolmogorov-Smirnov test. Categorical variables will be described as frequencies and percentages. Measures of central tendency will be compared using the T-test for independent samples or ANOVA, or their non-parametric counterparts: the Mann-Whitney U and Kruskal-Wallis tests. Categorical variables will be compared using the Chi-square test or Fisher’s exact test. If post hoc analyses are performed, the Bonferroni or the Games-Howell adjustments will be applied. Variables with differences in the bivariate analysis at baseline (*p* < 0.1) and those considered clinically relevant for the authors will be included in a linear multiple logistic regression to build a multivariate model to predict the difference in mean days of hospital stay and costs of patients in the HC program. To address Better Care and Better Health endpoints, the authors will apply a binary logistic regression for mortality and hospital admission variables; age, gender, and comorbidity burden will be included as adjustment variables. A backward stepwise regression will be used to avoid overfitting of the model obtained.

A significance threshold will be set at two-sided alpha value < 0.05. The analysis will be performed with SPSS (IBM Corp. Released 2012. IBM SPSS Statistics for Windows, Version 21.0. Armonk, NY: IBM Corp.).

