## Discussion

Since life expectancy of the population is increasing in developed countries, healthcare policymakers are prompted to tailor healthcare services to the specific needs of older people. In this context, the local healthcare authorities in Badalona (Spain) decided to change from a integrated HC model to a functional HC model, in which preventive home visits are provided by a dedicated healthcare team, different from that looking after patients in primary care units. Although various models of functional care have been proposed to prevent unnecessary hospitalizations and contribute to better health outcomes in post-acute patients [15, 16, 42], different populations and healthcare settings make it necessary to assess the outcome of this change in our area.

The main strengths of the functional model include a faster response to emergencies and the specialization of healthcare professionals. On the other hand, a potential disadvantage of this model —compared with the integrated one— is that it breaks the continuity of care (i.e., the patient is attended by a different healthcare team in the primary care unit and at home). Despite this limitation, the functional model is expected to yield better outcomes. In addition to the comparative analysis between both models, previous experiences in similar populations from our area will serve as a reference to interpret the results obtained [43, 44].

An important strength of this study is the homogeneity of both study groups. The quasi-experimental design precludes an active selection of the study sample, which is naturally defined by patients attending one of the primary care units based on their location. However, the characteristics of the reference population of both centers are very similar in terms of age and complexity (measured using the GMA risk [21, 45, 46]), suggesting that the baseline characteristics of study patients are likely to be balanced at the end of the study. Furthermore, unlike other change assessments in the HC model, this study will capture data prospectively, thus favoring the accuracy of the final record.

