On the other hand, some limitations can be predicted. Firstly, a possible Hawthorne effect, according to which the quality of care may improve due to the fact that healthcare professionals are being assessed [47] cannot be ruled out. To our understanding, this effect —in case it occurs— is likely to decline throughout follow-up. Secondly, it seems almost unavoidable that patients will fail to report the use of private facilities, a fact that shall be considered at the moment of reporting results. Finally, this study has a risk of unbalanced reporting bias due to the differences in the healthcare teams of each model. Specifically, whereas in the integrated HC group multiple observers will contribute to data capture, in the functional group all assessments will be performed by a single HC team. In this regard, the reporting bias is likely to be attenuated in the integrated group by the presence of multiple observers, but not in the functional group. To increase homogeneity in practices and data recording, all investigators will receive a brief training.

In summary, the proposed study will permit assessment of health outcomes, feasibility, and resource utilization of new functional HC model and identify its strengths and weaknesses compared to the integrated model. The results obtained from this study may have important policy implications.

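### With one centre per model, alpha and power describe the difference between two centres; they extend to the two models only if there is no between-centre variance

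*Protocol article*

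**What the plan says.** The Study design section says that the study will "compare the outcome of two HC models implemented in two primary care centers in Badalona (Barcelona, Spain", and it assigns one centre to each arm. "The control group will consist of patients following the integrated HC model, provided by the primary care center" Gran Sol; the study group comes from Apenins. The Discussion says that the sample is one "which is naturally defined by patients attending one of the primary care units based on their location", so membership follows residence and is not decided patient by patient. It also says that "in the functional group all assessments will be performed by a single HC team".

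The Statistical analysis section sizes the study as two groups of independent patients (40% admission incidence, a reduction of 10%, alpha and beta of 5%, 581 per group) and adds: "The statistical power of this sample, assuming alpha and beta errors of 5% was 85.3" (per cent). The tests are at patient level: "Measures of central tendency will be compared using the T-test for independent samples or ANOVA", or their rank-based counterparts, chi-square or Fisher tests, and regressions adjusted for patient characteristics. No centre-level variance appears in the sample size or in the tests.

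Study design justifies the choice of centres by demographic balance. The Discussion goes further: "An important strength of this study is the homogeneity of both study groups". The limitations it lists are a Hawthorne effect, unreported private care, and a single observer team versus several. Confounding of model with centre is not among them.

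**The concern.** The stated aim is to compare two models of home care, and the Discussion expects policy implications. Centres can differ in hospital days for reasons unrelated to the model, for example referral habits, access to beds, local social support or the skill of one particular team. With one centre per model, any such difference enters the estimated model effect in full and is absent from its standard error. Adjustment for age, sex and comorbidity can remove measured case-mix differences but not a difference that belongs to the centre. A significant result could then be read as evidence for or against the functional model when it shows only that Apenins and Gran Sol differ.

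**Working it through.** **Structure (no assumed figure needed).** There are two centres and two models, one centre per model. Between-centre degrees of freedom are 2 − 2 = 0. A centre term cannot be fitted beside the model term, and the ICC cannot be estimated from the study.

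**The plan's own sample size.** Inputs from Statistical analysis: 40% v 30% (10% read as absolute), two-sided alpha 5%, power 95%, 1:1.

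n = [1.96·√(2·0.35·0.65) + 1.645·√(0.4·0.6 + 0.3·0.7)]² / 0.10² = (1.322 + 1.104)² / 0.01 ≈ 589 per group.

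The unpooled version gives 585. The stated 581 is within 3%, so it is a calculation for independent patients with no design effect. Power at 581 is 94.8%, not 85.3%.

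**Patients likely to be available.** Background: home care programmes enrol 5% of people over 65. Table 2: 3480 and 2970 people aged 65 or over. So 0.05·3480 = 174 and 0.05·2970 ≈ 149, before exclusions and refusals.

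**Illustration of type I error, admission endpoint.** The ICC is assumed, range 0.001 to 0.01.

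DE = 1 + (m − 1)·ICC; true alpha = 2·[1 − Φ(1.96/√DE)].

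| ICC (assumed) | DE, m = 150 | True alpha, m = 150 | DE, m = 581 | True alpha, m = 581 |
|---|---|---|---|---|
| 0 | 1.00 | 5.0% | 1.00 | 5.0% |
| 0.001 | 1.15 | 6.7% | 1.58 | 11.9% |
| 0.005 | 1.75 | 13.8% | 3.90 | 32.1% |
| 0.01 | 2.49 | 21.4% | 6.80 | 45.2% |

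**What these ICCs mean.** At ICC 0.01 the between-centre SD is √(0.01·0.35·0.65) = 4.8 percentage points, so the gap between two centres has an SD of 4.8·√2 ≈ 6.7 points, about two thirds of the 10-point planning effect. At ICC 0.001 the between-centre SD is 1.5 points.

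**The same point without an ICC.** Take a fixed non-model gap d in admissions and no model effect. The rejection rate is Φ(d/SE − 1.96) + Φ(−d/SE − 1.96), with SE = √(2·0.35·0.65/m).
- m = 581, SE = 0.0280: 18.8% for a 3-point gap, 43.1% for a 5-point gap.
- m = 150, SE = 0.0551: about 8% (Φ(−1.415) + Φ(−2.505)) and about 15% (Φ(−1.052) + Φ(−2.868)).

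**Balance claim against Table 2.**

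| Row | Gran Sol | Apenins | P |
|---|---|---|---|
| Over-aging index | 11% | 9.2% | < 0.001 |
| Foreign population | 17.9% | 15.9% | < 0.001 |
| Aged 65 or over | 17.9% | 15.6% | < 0.001 |
| GMA | 1.189 (1.173–1.206) | 1.178 (1.161–1.195) | not given |
| Annual mortality, per thousand | 7 | 5.7 | 0.143 |

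The Discussion calls the reference populations very similar in age and complexity. Complexity (GMA) is close, but two of the three rows with P < 0.001 concern age. The table describes whole reference populations, not home-care patients or hospital use.

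**The case against.** The article calls itself quasi-experimental and a pilot, says that groups follow location, and concedes one source of bias from single versus multiple teams. Two models already running in two centres is a known design limit that no analysis can remove. The centres share a town, public coverage, IT application and care protocols. GMA intervals overlap, mortality does not differ significantly, and with about 19,000 people per centre small differences reach P < 0.001. Adjustment will deal with part of the measured case mix. All of this is fair, and it makes a large centre effect less likely. It does not make the effect zero. The quasi-experimental label admits non-randomisation, not a single cluster per arm.

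Some stronger readings are tempting but not supported:
- **That a false policy conclusion is likely.** The documents give no between-centre variance, so this is a material risk of unknown size.
- **That the error rate is 12% to 45%.** That needs 581 patients per centre, which the 5% enrolment figure makes implausible.
- **That these figures measure the error for the primary endpoint.** They concern admissions; the endpoint is mean hospital days per year.
- **That the centre effect explains why 85.3% fails.** It is wrong for 581 per group with no centre effect at all. The conflict between 85.3% and the 95% implied by beta of 5%, and the sizing on admissions rather than hospital days, are separate faults.

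**Conclusion.** The point holds as a matter of identification: the model effect cannot be separated from the centre effect, and the stated alpha and power carry over to the model comparison only if between-centre variance is zero. That conclusion rests on the protocol's own description and needs no assumed number. The size does need one. Under an assumed ICC of 0.001 to 0.01, type I error for admissions is about 7% to 21% at a realistic 150 per centre and about 12% to 45% at 581; for hospital days it is unknown. The article is also wrong as written in offering balance and homogeneity as a strength, since three rows of its own Table 2 show P < 0.001, and in leaving this confounding out of its limitations.

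**What to change.** 1. **Statistical analysis:** state that p-values, intervals and power describe the difference between these two centres, and hold for the models only on the assumption of no between-centre variance. Give the illustrative range, labelled as resting on an assumed ICC and on admissions.
2. **Discussion, limitations:** add confounding of model with centre and limit the policy conclusion to match.
3. **Study design and Discussion:** withdraw the claims that the centres are balanced and that homogeneity is a strength, and report the Table 2 differences as they stand.
4. **Conditional and supportive only:** if there was a period before the functional model at Apenins, and hospital days for it can be retrieved under ethics approval, report a difference-in-differences estimate. Say that it removes only stable centre differences and still rests on two clusters.

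Items 1 to 3 cost only text and a more cautious claim. Item 4 needs a feasibility check first: the documents give no start date for the functional model, do not say that eCAP holds past hospital days, and describe consent only for current participants. It would not restore a valid 5% level.
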